#### Safety analyses

All AEs occurring during this study will be listed and the incidence of AEs will be calculated. The χ2 test or Fisher's exact test will be used to compare the incidence of AEs among groups. As for the laboratory indexes, the frequency table and specific situation of changes will be listed.

#### Subgroup analyses

The absolute value of blood eosinophils will be used as a stratification factor to perform the stratification analysis of the efficacy indicators. The efficacy indicators will also be analyzed by TCM constitution, if possible. The assessment of TCM constitution is based on the Classification and Determination of Constitution in TCM(ZYYXH/T157-2009) released by the China Association of Chinese Medicine.

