Traditional Chinese Medicine (TCM) is the greatest treasure trove waiting to be discovered by modern medicine. YuPingFeng (YPF), one of the classic TCM formulas with a tonic effect, is composed of Astragali Radix, Atractylodes Macrocephala Koidz, and Radix Saposhnikoviae. Recent pharmacological studies have shown that YPF can activate mucosal immunity, resists hormone-induced immunosuppression, and is recommended to be used in the treatment of stable COPD [13, 14]. A multicentre, randomized, double-blind, placebo-controlled clinical study we conducted confirmed that the combination of conventional treatment with YPF granules for 52 weeks significantly reduced the risk of acute exacerbations by 32.3% in moderate-to-severe COPD patients [15], but did not investigate the mechanism. Some small sample sizes or observational trials have shown that this drug may regulate immune function, improve lung function, and improves the quality of life [16, 17], but high-quality evidence-based evidence is still lacking. In recent years, the heterogeneity of AECOPD has been gradually recognized and preliminarily explored. The clinical phenotype differentiated by peripheral eosinophils is one of the important phenotypes of AECOPD. Eosinophils are generally considered to be a type of white blood cell associated with allergic diseases. In allergic disease, YPF has been shown to have good effects in both improving symptoms and controlling relapses [18–20]. A number of studies have also shown that YPF inhibits eosinophil activity and also inhibits eosinophil proliferation [21, 22]. We hypothesized that YPF may have a more pronounced clinical benefit on the eosinophilic phenotype of AECOPD. Therefore, we designed a prospective, multicentre, randomized, double-blind, placebo-controlled clinical trial based on eosinophil phenotypic stratification to evaluate the efficacy of YPF on clinical symptoms and quality of life, safety, and therapeutic response in microecology and immunity in stable COPD. We hoped to confirm the preventive and trerapeutic effects of YPF from different perspectives and to discover its possible mechanism.

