### Sample size

According to the results of the previous study [15], the mean difference in CAT scores between the YPF group and the control group was 2.2, and the combined standard deviation was 6.2184. The sample size was calculated accordingly, with an α risk of 0.05 and a β risk of 0.2 in a two-sided contrast. This study required a minimum of 252 subjects. Allowing for 20% attrition, a total sample size of 316 subjects was required, 158 in the treatment group and 158 in the control group.

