### Statistical analysis

The SAS 9.4 statistical software will be used for statistical analysis. Both full analysis set (FAS) and per-protocol set (PPS) will be used for baseline and efficacy analysis, while the safety set (SS) for the safety analysis. Data will be descriptively analyzed and presented as means and standard deviations, medians and interquartile ranges, and frequencies. The minimum, maximum, P25, median, and P75 are given when necessary. All analyses will be two-sided, with a *p*-value of less than 0.05 considered statistically significant.

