In this study, we will also perform stratified analysis. Firstly, clinical studies have indicated that peripheral blood eosinophils are a biomarker of exacerbation risk in patients with a history of exacerbations and may be useful in guiding inhaled corticosteroids (ICS) treatment in patients at high risk of AECOPD at stable stage [40, 41]. It was also confirmed that YPF had resistance to hormone-induced immunosuppression. Therefore, stratification based on absolute values of blood eosinophils can explore whether there is a difference in the clinical efficacy of YPF on COPD eosinophilic phenotype and non-eosinophilic phenotype, which is instructive for YPF combined with hormonal treatment of COPD. Secondly, as YPF is a classical prescription, this study will conduct a stratified analysis by TCM constitution, which is in line with the clinical practice of TCM use. This study is a randomized, double-blind, placebo-controlled, multicenter clinical trial with a long intervention duration of 52 weeks, which is also consistent with the characteristics of TCM intervention for chronic diseases. However, long-term medication might affect patient compliance, and the collection of biological samples has time requirements, which requires high compliance. Second, the study included patients with moderate-to-severe COPD, which may not represent all COPD patients, especially those with early COPD. Whether YPF is suitable for the health management of COPD requires further clinical evaluations in different COPD populations.

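### The trial is built around a larger YPF benefit in the eosinophilic phenotype, but the analysis stated for it contains no comparison of the effect between strata

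*Protocol article*

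**What the plan says.** The Background gives the hypothesis: "We hypothesized that YPF may have a more pronounced clinical benefit on the eosinophilic phenotype of AECOPD". It describes the design as resting on stratification by eosinophil phenotype. Under Randomization, blinding and unblinding, the blood eosinophil count at enrolment, cut at 0.3 × 10^9/L, is the only stratification factor named. The Discussion says that stratifying "can explore whether there is a difference in the clinical efficacy of YPF on COPD eosinophilic phenotype and non-eosinophilic phenotype", and that the answer would inform use of YPF alongside hormonal treatment.

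The analysis is one sentence under Subgroup analyses: "The absolute value of blood eosinophils will be used as a stratification factor to perform the stratification analysis of the efficacy indicators". The next sentence adds an analysis by TCM constitution, if feasible. Efficacy analysis names Fisher's exact test for rates and proportions. For changes in CAT, SGRQ and symptom scores it names the log-rank test and a Cox model. The general rule is: "All analyses will be two-sided, with a *p*-value of less than 0.05 considered statistically significant". No treatment-by-stratum term or other between-stratum comparison appears in the article.

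**The concern.** The hypothesis concerns a difference between two treatment effects. The wording under Subgroup analyses has two natural readings, and neither estimates that difference:

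- **Stratum-adjusted analysis.** This pools the effect over strata and gives one answer for everyone.
- **Repetition of the efficacy tests within each stratum.** This gives two p-values, each against no effect, and no comparison of one effect with the other.

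Of the named methods, Fisher's exact and the log-rank test give no interaction estimate. A Cox model could carry an interaction term, but the article uses it only to obtain a hazard ratio and its interval.

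The comparison motivated the stratified design and is offered as informative for practice. If all that is available at the end is one significant and one non-significant stratum, readers may take that as evidence for or against an eosinophilic responder group.

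**Working it through.** **Inputs.** From Sample size: "the mean difference in CAT scores between the YPF group and the control group was 2.2, and the combined standard deviation was 6.2184"; "with an α risk of 0.05 and a β risk of 0.2 in a two-sided contrast"; "This study required a minimum of 252 subjects". Allocation is 1:1 (Study design). The share of patients above the cut-off is not given. It is assumed to be 20–40%, with the same SD and 1:1 allocation in both strata.

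**The plan's own figure.** n per arm = 2(1.960 + 0.842)² × 6.2184² / 2.2² = 2 × 7.849 × 38.669 / 4.84 = 125.4, so 126 per arm and 252 in total. With 20% attrition, 126 / 0.8 = 157.5, so 158 per arm and 316 in total. Both stated figures are reproduced.

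**Separate tests, identical true effect of 2.2 points in both strata.** With n patients per arm in a stratum, SE = 6.2184 × √(2/n), and power ≈ Φ(2.2/SE − 1.96), the opposite tail being negligible. With powers pH (high eosinophils) and pL (low):

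- only the eosinophilic stratum significant: pH(1 − pL)
- only the non-eosinophilic stratum significant: pL(1 − pH)
- exactly one significant: the sum of the two

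Example at a 20% share: nH = 0.2 × 126 = 25.2 and nL = 100.8 per arm. SE is 1.75 and 0.88, so pH = 0.241 and pL = 0.709. Only eosinophilic: 0.241 × 0.291 = 0.070. Only non-eosinophilic: 0.709 × 0.759 = 0.538. Sum: 0.608.

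**Interaction.** SE = 6.2184 × √(2/nH + 2/nL). The difference detectable with 80% power is 2.80 × SE.

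| Share high | pH | pL | Only eosinophilic | Only non-eosinophilic | Exactly one | Interaction SE | Detectable difference |
|---|---|---|---|---|---|---|---|
| 20% | 0.241 | 0.709 | 0.070 | 0.538 | 0.608 | 1.96 | 5.49 |
| 30% | 0.337 | 0.652 | 0.117 | 0.432 | 0.549 | 1.71 | 4.79 |
| 40% | 0.427 | 0.585 | 0.177 | 0.335 | 0.512 | 1.60 | 4.48 |

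Non-central t powers (0.23–0.42 high, 0.71–0.58 low) move only one end of these ranges: the maximum for only non-eosinophilic becomes 0.71 × 0.77 = 0.55.

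**Sensitivity.** Over shares of 15–50%, exactly one stratum is significant with probability 0.500–0.645, and the detectable difference is 6.15–4.39 points. With all 158 per arm evaluable, the figures are 0.478–0.676 and 5.49–3.92 points.

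**Other cases.** With no effect in either stratum, exactly one is significant with probability 2 × 0.05 × 0.95 = 0.095 per endpoint. An interaction test at two-sided 0.05 has a 5% error rate by construction. Its power for a between-stratum difference of 2.2 points is 20% at a 20% share and 28% at a 40% share.

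**The case against.** The strongest reply is that this reads too much into one sentence of a condensed article. Subgroup analyses names no test and no rule for reading results, and subgroup modelling is often left to an analysis plan, which is not shown here. The 0.05 level would apply equally to an interaction test. The Discussion speaks of exploring, not of declaring.

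Much of this stands. A reader might infer that the trial will claim a phenotype-specific effect from one significant and one non-significant stratum. The article does not say so, and the probabilities above apply only if that were done. Nor is most of the 51–61% false support for the hypothesis. The larger part (34–55%) would wrongly count against it, and only 7–18% would wrongly favour it. Unequal strata are not the main cause either: with equal strata, discordance is still 50%.

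The reply does not remove the mismatch. The article states the hypothesis, ties the design to it, and then states an analysis. On both natural readings that analysis leaves the hypothesis untested, and nothing else in the text supplies the comparison. That is more than an omitted modelling detail.

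**Conclusion.** The point holds as a mismatch between the stated hypothesis and the stated analysis, and the text should be amended. It does not show that a false phenotype claim is planned, and it does not affect the overall comparison of YPF with placebo.

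The size is conditional. Discordance of about 51–61% under a common effect requires that the strata be tested separately and the p-values contrasted. It rests on the assumed 20–40% share, on equal SD and 1:1 allocation within strata, and on the mean-difference scale of the sample-size calculation. It does not describe the log-rank and Cox analysis that the article names for CAT change.

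The proper comparison is imprecise. Its SE of 1.6–2.0 points means that only between-stratum differences of about 4.5–5.5 CAT points are detectable with 80% power, at least twice the 2.2-point effect for which the trial was sized.

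**What to change.** Under Subgroup analyses, state that:

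1. the eosinophil question is judged by the treatment-by-eosinophil-stratum interaction estimate with 95% CI for the primary outcome, the week-52 CAT change, on the mean-difference scale used for the sample size;
2. results within eosinophil strata, and by baseline TCM constitution, are descriptive and carry no separate significance claims (baseline needs saying, because constitution is measured again at weeks 24 and 52 and its change is a secondary outcome);
3. the comparison is exploratory, because the sample size was not set for it and only differences of about 4.5–5.5 points are detectable with 80% power.

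The cost is one extra model term, a few sentences and a less favourable statement of precision. No new data are needed. The term belongs in a model of mean CAT change, which Efficacy analysis does not currently name, so that section must agree with it. The fix is confined to the primary outcome because the article names Fisher's exact test for exacerbation rates, which leaves no rate model to extend.

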### Safety and ethics

YPF has been used clinically for many years and has good safety in the preliminary study [15]. To ensure the safety of subjects, all subjects are given YPF or placebo treatment in addition to routine therapy and will be received relevant safety checks. Investigators will also take timely symptomatic treatment of AEs in the subjects. Before enrollment, investigators will inform the subjects about the details of the trial, including the purpose, methods, procedures, possible benefits, and risks, and answer any questions the subjects may have. Subjects will not perform any study procedures until they have voluntarily signed the written informed consent form. They can withdraw from the trial at any time without damage during the trial. If the protocol or informed consent is significantly modified, we will re-submit the ethics for approval and reacquire the consent of the subjects again.

### Dissemination

No data will be provided to any third party in any form without the written consent of the sponsor. All data and analysis will remain blinded until the results are published. The final results will be published in relevant journals in the form of literature.

## Discussion

The management of stable COPD is a complex clinical challenge, and the 2022 GOLD guideline states that the aim of management is to reduce both current clinical symptoms and the risks of future exacerbations. In particular, AECOPD directly poses a serious threat to life. In our previous clinical study [15], we confirmed that YPF reduces the risk of AECOPD, but there was a lack of high-quality evidence of symptom reduction and quality of life improvement. COPD is a progressive and debilitating respiratory disease, characterized by dyspnea and irreversible airflow restriction. Most COPD patients experience various symptoms at the same time, such as dyspnea, sleep disturbance, fatigue, etc. At the same time, different symptoms synergistically damage the quality of life, functional status, and psychological status of patients. Among them, 64.2% of COPD patients report that dyspnea impaired their quality of life, and COPD patients with depression, anxiety, and fatigue show the poorer quality of life [25]. In this trial, we design a clinical symptom assessment scale including cough, expectoration, fatigue, etc., to standardize the evaluation of each common clinical symptom of COPD. At present, the SGRQ is considered to be the most effective scoring system for evaluating quality of life in COPD patients. However, the conversion method of the SGRQ is complex, and the content is numerous and time-consuming, making it difficult for some patients to complete independently. The CAT is simple in structure, easy to operate, and short in time, which is more suitable for patients with limited education and low compliance than SGRQ. So we are using the two questionnaires in this trial, with the changes in the CAT score after 52-week of treatment as the primary outcome, and the clinical symptoms and the SGRQscores as the secondary outcomes, and we hoped that the results will be mutually confirming and complimentary.

Microbiota is defined as the “ecological community of commensal, symbiotic and pathogenic organisms that share our body space” [26]. In recent years, with the application of various new techniques (such as NGS) to detect microbes, increasing evidence indicates that respiratory and intestinal microbiota and their associated mucosal immunity are related to the clinical manifestations, acute exacerbations, and prognosis of COPD [27–32]. Studies have showed that the pulmonary microbiota also changes during AECOPD compared to stable condition samples [33–37]. Pulmonary microbial composition was transferred to *Proteobacteria*, while Firmicutes decreased [33]. Manifested by an increase in *Hemophilus influenza* and a decrease in the relative abundance of *Streptococcus pneumonia* species [34]. In addition, there was a significant increase in Moraxella catarrhalis, and this species was positively correlated with the percentage of neutrophils in sputum, suggesting the possibility of interaction between host immune response and microbiome [33]. A case–control study showed that there was a strong and independent relationship between the presence of peptic ulcer disease and lung function indices in COPD patients with peptic ulcer disease [30]. Animal studies have indicated that gut microbiota and high-fiber diets play a role in the pathogenesis of COPD in smoking-exposed mice [38, 39]. Therefore, in this study, biological samples including blood and sputum will be collected to evaluate the therapeutic response of YPF in stable COPD from the perspective of microecology and immunity, and to explore the mechanism of YPF in reducing the risk of AECOPD.

In this study, we will also perform stratified analysis. Firstly, clinical studies have indicated that peripheral blood eosinophils are a biomarker of exacerbation risk in patients with a history of exacerbations and may be useful in guiding inhaled corticosteroids (ICS) treatment in patients at high risk of AECOPD at stable stage [40, 41]. It was also confirmed that YPF had resistance to hormone-induced immunosuppression. Therefore, stratification based on absolute values of blood eosinophils can explore whether there is a difference in the clinical efficacy of YPF on COPD eosinophilic phenotype and non-eosinophilic phenotype, which is instructive for YPF combined with hormonal treatment of COPD. Secondly, as YPF is a classical prescription, this study will conduct a stratified analysis by TCM constitution, which is in line with the clinical practice of TCM use. This study is a randomized, double-blind, placebo-controlled, multicenter clinical trial with a long intervention duration of 52 weeks, which is also consistent with the characteristics of TCM intervention for chronic diseases. However, long-term medication might affect patient compliance, and the collection of biological samples has time requirements, which requires high compliance. Second, the study included patients with moderate-to-severe COPD, which may not represent all COPD patients, especially those with early COPD. Whether YPF is suitable for the health management of COPD requires further clinical evaluations in different COPD populations.

## Data Availability

Not applicable.

## Abbreviations

COPD: Chronic obstructive pulmonary disease
WHO: World Health Organization
AECOPD: Acute exacerbation of COPD
TCM: Traditional Chinese medicine
YPF: YuPingFeng
SGRQ: The St George's Respiratory Questionnaire
CAT: COPD assessment test
HCG: Human chorionic gonadotropin
NGHX: Urine dry chemical analysis
eCRF: Electronic case report form
SAS: Statistical Analysis System
ECG: Electrocardiogram
FAS: Full analysis set
PPS: Per-protocol set
SS: Safety set
AE: Adverse event
CRO: Contract research organization
CMP: Clinical monitoring plan
CRA: Clinical research associate
EDC: Clinical trial electronic data capture system
